#### Collection of patient-reported outcomes and quality of life

Vaccine hesitancy will be collected at the time of enrolment using the Oxford COVID-19 Vaccine Confidence and Complacency Scale [41]. Quality of life will be assessed at multiple timepoints using the validated EORTC QLQ-C30 tool for adults, and the PedsQL measurement model for children [42, 43]. Patient-reported adverse effects will be collected 7 days after each vaccine dose using an online survey sent by email or text message, or paper survey comprising of Patient Reported Outcome- Common Terminology for Adverse Events (PRO-CTCAE) [44] items relevant to vaccine related adverse effects. Additional items of interest regarding delays in cancer treatment and hospital admissions will also be collected. The schedule is included in Table 3 and the full list of PROCTCAE items are listed in Additional file 3: Appendix S3.

**Table 3 Tab3:** Patient reported outcomes and quality of life

	EORTC QLQC30 or PedsQL	Hesitancy scale	PRO CTCAE	Toxicity^a^
Vaccine dose 1 (− 7)	X	X		
D7 (± 1) post dose 1	X		X	
Vaccine dose 2	X			
D7 (± 1) post dose 2	X		X	
3 M post dose 2	X			X

*D* day, *M* month, *EORTC QLQ* European Organisation for Research and Treatment of Cancer Quality of Life Questionnaire, *PRO CTCAE* Patient Reported Outcomes Common Terminology Criteria for Adverse Events

^a^Medical record review

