## Methods

### Study design

The SerOzNET study objective is to characterise the response of patients with cancer, including children, to the currently available COVID-19 vaccinations in Australia. The aims of the study are to evaluate serologic and immunological responses to COVID-19 vaccination in predefined cohorts of patients with cancer in Australia, to evaluate short- and medium-term safety of COVID-19 vaccination in patients with cancer, and to evaluate the effect of COVID-19 vaccination on patient-reported quality of life.

SerOzNET is a multi-arm, multi-centre, prospective, observational cohort study of patients with cancer undergoing routine COVID-19 vaccination. Control samples will be provided by healthy controls enrolled on concurrent, separate studies with collaborating investigators, with blood tests taken at harmonised time points for comparison. Time points for sampling have also been harmonised with the publicly shared “SeroNet” protocol template released by the United States National Cancer Institute (NCI) to allow international comparisons [40]. To provide a nuanced understanding of outcomes depending on patient characteristics, this study will enrol patients falling into specific treatment cohorts and collect detailed demographic information.

Hypotheses:The anamnestic humoral response to COVID-19 vaccine is likely to be blunted in cancer patients due to immunosuppression arising from their disease and/or treatment.The T-lymphocyte-mediated vaccine response may also be modulated due to disease and treatment factors, with the impact of contemporary treatments such as immune checkpoint inhibitors of particular interest.The adverse event profile may differ in cancer patients compared with the non-cancer population and therefore the impact of vaccine administration on quality of life of cancer patients is unknown.

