The endpoints of SerOzNET relate to these hypotheses. The core primary endpoint is seroconversion rate following COVID-19 vaccine in each cohort compared with healthy controls at 1 month post second dose. Co-primary endpoints are translational research into immune correlates of COVID-19 vaccine in each of the cancer cohorts compared with healthy controls (qualitative and quantitative measures of humoral and cellular immunity) and assessment of patient-reported and medically determined adverse effects and quality of life following vaccination. Secondary endpoints include exploratory analysis of further immunologic parameters to characterise vaccine response and investigation of durability and kinetics of response in the months post vaccination.

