### Setting

The SerOzNET lead study site is an outer-urban hospital in south-east Melbourne, Victoria with a large oncology department located over several campuses serving a culturally and linguistically diverse population. Patients will be approached during the course of their routine cancer care by a member of their care team (such as oncologist, haematologist, or nurse); further study advertisement will be via posters in waiting rooms and day treatment units which can facilitate self-referral. COVID-19 vaccination (standard of care, product administered dependent on current guidelines and availability) will occur at either a state-run site or local general practice according to availability and is not administered as part of the study itself: this approach was chosen so as to not complicate the running of the vaccine clinics or present confusion about responsibility for management of any acute toxicities. Study participants will attend the lead site at several timepoints relative to their COVID-19 vaccine for biospecimen collection. Surveys and scales for patient-reported quality of life and adverse events will be offered to patients preferably via email or SMS to complete remotely or via tablet while on-site, but for those without internet access paper surveys will be given.

Healthy controls are enrolled on parallel studies with collaborating investigators. Timepoints for blood collection and planned assays have been harmonised with the healthy control studies to allow direct comparison of outcome.

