#### Toxicity

Apart from patient-reported outcomes, a medical review of records 3 months after the second dose of vaccine will be conducted to capture any serious adverse events as well as adverse events of interest (for example: delays in cancer treatment, blood clots, lymphadenopathy on imaging requiring further follow up). The database entry fields for this are presented in Additional file 1: Appendix S1.

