### Sample size and statistical analysis

The sample size of 100 per cohort will have over 80% power (β of 0.80) to detect a decrease of 10% seroconversion rate in any cancer cohort (compared with assumed non-cancer population incidence of 95%) with 95% confidence (α of 0.05). T-lymphocyte correlates of vaccine response are less well-defined than the expected seroconversion rate, therefore this analysis has not been subject to formal statistical planning and comparison between groups via t-tests or analysis of variance will be for the purpose of hypothesis generation, with significant results deemed to be p < 0.05. Patient reported and medically reported toxicity will be analysed descriptively. Patient-reported quality of life will be analysed longitudinally.

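### PRO-CTCAE is scheduled only 7 days after each dose, so item-level symptom rates will mix background cancer and treatment symptoms with vaccine effects

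*Protocol article*

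**What the plan says.** The section on collection of patient-reported outcomes sets the timing: "Patient-reported adverse effects will be collected 7 days after each vaccine dose using an online survey sent by email or text message" (or a paper form). It then refers the reader on: "The schedule is included in Table 3 and the full list of PROCTCAE items are listed in Additional file 3: Appendix S3".

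Table 3 marks the instruments as follows:

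| Time point | QLQ-C30 or PedsQL | PRO-CTCAE |
|---|---|---|
| Dose 1 (window of 7 days before) | yes | no |
| Day 7 after dose 1 | yes | yes |
| Dose 2 | yes | no |
| Day 7 after dose 2 | yes | yes |
| 3 months after dose 2 | yes | no |

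The Study design section makes these data part of the co-primary endpoints: "assessment of patient-reported and medically determined adverse effects and quality of life following vaccination". The related hypothesis begins: "The adverse event profile may differ in cancer patients compared with the non-cancer population". The planned analysis is one sentence: "Patient reported and medically reported toxicity will be analysed descriptively".

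The other safety source is in the Toxicity section: "a medical review of records 3 months after the second dose of vaccine will be conducted to capture any serious adverse events", together with events of interest. On controls, the Setting section says: "Timepoints for blood collection and planned assays have been harmonised with the healthy control studies to allow direct comparison of outcome".

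**The concern.** Several cohorts in the Participants section are on active treatment at vaccination: cytotoxic chemotherapy, checkpoint inhibitors, endocrine or targeted therapy. Some will have symptoms in any given week, whether vaccinated or not. A symptom reported at day 7 may be new, worsened, or unchanged from the week before, and a single post-dose score does not show which.

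Two things are at stake. First, item-level rates may be read as vaccine adverse effects when part of each rate is background. Second, a difference between cohorts may reflect how symptomatic their treatments are, not how they tolerate the vaccine. The allergy cohort adds weight, because its data are analysed for safety only unless the participant also belongs to another cohort. The Discussion hopes that the safety data will reassure hesitant patients, and counting background symptoms as vaccine effects would work against that.

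The article fixes this schedule itself in both text and table. It is not a detail left to an analysis plan, and no analysis plan can recover a baseline that was not collected.

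**Working it through.** The article gives no figure to reproduce here: no background symptom rate, no expected adverse-effect rate and no precision target for toxicity. The check has two parts.

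**1. Is there a substitute baseline or comparator for the PRO-CTCAE items?**

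- *QLQ-C30 or PedsQL.* It is collected at both dose visits and analysed longitudinally: "Quality of life will be assessed at multiple timepoints using the validated EORTC QLQ-C30 tool for adults, and the PedsQL measurement model for children". It shows change in quality of life and in symptoms that both instruments cover. It is a different instrument, so a PRO-CTCAE item score cannot be differenced against it.
- *Day 7 after dose 1, as baseline for dose 2.* This score follows vaccination.
- *Record review.* It takes place 3 months after dose 2 and targets serious events and events of interest. It supplies no pre-dose symptom score.
- *Healthy controls.* Harmonisation is described for blood time points and assays. PRO-CTCAE collection in controls is neither stated nor excluded.

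None of these gives a pre-dose value for the PRO-CTCAE items.

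**2. How much could this matter?**

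Let *b* be the background prevalence of a symptom, *v* the vaccine-induced rate among patients otherwise symptom-free, and *obs* the day-7 prevalence. If the two sources are independent (an assumption):

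obs = 1 − (1 − b)(1 − v), so v = 1 − (1 − obs)/(1 − b).

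The values of *b* and *obs* are assumptions, shown as a range.

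| obs | b | v |
|---|---|---|
| 50% | 0% | 1 − 0.50/1.00 = 50% |
| 50% | 20% | 1 − 0.50/0.80 = 37.5% |
| 50% | 40% | 1 − 0.50/0.60 = 16.7% |
| 50% | 50% | 1 − 0.50/0.50 = 0% |
| 30% | 0% | 1 − 0.70/1.00 = 30% |
| 30% | 10% | 1 − 0.70/0.90 = 22.2% |
| 30% | 20% | 1 − 0.70/0.80 = 12.5% |
| 30% | 30% | 1 − 0.70/0.70 = 0% |

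For scale, the 95% sampling error of a proportion in a full cohort of 100 is 1.96 × √(0.5 × 0.5/100) = 9.8 points at 50% and 1.96 × √(0.3 × 0.7/100) = 9.0 points at 30%. The range of *v* compatible with one observed rate can far exceed this, and a larger cohort would not narrow it.

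The same formula shows the effect on cohort comparisons. Take two cohorts with the same *v* of 16.7%. With *b* = 40%, obs = 1 − 0.60 × 0.833 = 50%. With *b* = 20%, obs = 1 − 0.80 × 0.833 = 33.3%. The reported rates differ by 16.7 points although the vaccine effect is identical.

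**The case against.** The other side has a fair case on several points.

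- *The co-primary endpoint does have paired data.* Its quality-of-life part is measured at both dose visits and afterwards, and the Discussion says that toxicity and quality-of-life data will be linked. This stands. A reader might infer that the whole endpoint lacks a within-person baseline, which is wrong. The gap is confined to the PRO-CTCAE items, and the article gives no item-level method of linkage.
- *Control data may exist.* A reader might infer that no adverse-event comparison with non-cancer controls is planned. The Abstract speaks of using data from healthy controls in parallel studies, without limiting this to samples, and those studies are not shown. The documents support only that no such data are described.
- *Some cohorts are less affected by treatment.* Children treated without recent systemic therapy serve as controls, and the survivorship cohort finished chemotherapy 6 to 12 months earlier. Table 3 makes no exception for either. They give some indirect information on background, but they are not a pre-dose score for patients on treatment.
- *The survey may ask about attribution.* Its items are chosen for relevance to vaccine effects, and Appendix S3 is not shown. Wording such as new since vaccination cannot be excluded. It would help, though a patient's attribution is weaker evidence than a measured change.
- *The hypothesis is modest.* It says only that the profile may differ, goes on to quality of life, and is served by description, not a test. A reader might infer that it cannot be answered at all, or that cohort differences will mainly reflect treatment symptoms. Neither is shown: the first depends on unseen control data and survey wording, the second on background rates that the article does not give.

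None of this supplies a pre-dose score for the PRO-CTCAE items.

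**Conclusion.** The point holds in this limited form. Under the schedule as fixed, item-level PRO-CTCAE results will be prevalences 7 days after a dose, including background symptoms whose frequency may differ between cohorts. They should not be read as vaccine-attributable rates. This affects one component of a co-primary endpoint. Seroconversion, the immune assays and the quality-of-life analysis are untouched.

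The missing pre-dose assessment is certain from the text and Table 3. The size of the distortion is not known. In the illustration, an observed 50% is compatible with a vaccine-induced rate anywhere from 50% down to 0% as background rises from 0% to 50%. That range rests on assumed background rates and on independence of the two sources. Symptoms rarely caused by cancer treatment would be little affected, and common treatment symptoms could be strongly affected.

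The change is cheap enough that it should be made.

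**What to change.** 1. Add the same PRO-CTCAE items to the two surveys already scheduled at dose 1 (within the 7 days before) and at dose 2, for participants not yet dosed. State that they are completed before the injection.
2. Make the main patient-reported toxicity summary the proportion with a new or worsened symptom relative to the score before that dose, by item, dose and cohort. The raw day-7 prevalence can be shown beside it.
3. For participants already past dose 1, report day-7 results separately and label them as post-dose prevalence. A score at dose 2 can serve as a reference for change after dose 2, but not as a vaccine-naive baseline.
4. Limit the adverse-event hypothesis to within-person change unless comparable adverse-event data from controls are available. If they are, name the source, items and timing.

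The cost is a short extra questionnaire at two existing contacts, delivered through the same email, SMS, tablet or paper route. The baseline will be incomplete: the first participant was enrolled on 25 June 2021, and pre-dose scores cannot be recovered for those already vaccinated. The article reports recruitment as ongoing, so later participants can still provide them.

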#### Toxicity

Apart from patient-reported outcomes, a medical review of records 3 months after the second dose of vaccine will be conducted to capture any serious adverse events as well as adverse events of interest (for example: delays in cancer treatment, blood clots, lymphadenopathy on imaging requiring further follow up). The database entry fields for this are presented in Additional file 1: Appendix S1.

### Analyses

Serum and PBMCs will be used for a number of core analyses. Participants will be invited to consent during the SerOzNET participant consent process to the storage of excess biospecimens after these core analyses are complete, for later exploratory analyses to be guided by preliminary results from our study and evolving understanding of COVID-19 immunity worldwide.

Core analyses will comprise qualitative and quantitative serologic assays and T-lymphocyte immune cell assessment. Serologic neutralisation assays against clinically relevant variants of COVID-19 and immunochemical testing will be performed to detect the presence and titre of anti-SARS-CoV-2 spike protein as previously published, which is correlated with early post-vaccine protection against symptomatic COVID-19 infection [45, 46]. Variants will be selected based on the vaccine (the variant that is identical to the Spike antigen used), the most immune evasive (presently this is Beta) and the dominant circulating variant globally (presently this is Delta). As aliquots of serum will be stored, any emerging variants of concern can be further tested for antibody breadth against vaccine convalescent serum controls courtesy of other vaccine and cohort studies that are continuing in Australia.

Immune cell assessment of T-lymphocyte function derived from PBMC fraction will comprise phenotypic analyses of peripheral T cell subsets and functional assays to measure cytokine production (e.g., interferon γ, method previously published [47]) and cytotoxic responses (e.g., CD107a expression) after co-culture with antigen derived from SARS-CoV-2 via flow cytometry. Controls for co-culture experiments will include mitogenic stimulus and peptides derived from common viruses (such as cytomegalovirus, Epstein–Barr virus, or influenza antigen in patients who have received influenza vaccine). Correlation of magnitude of serological response and T-cell assays will be described within study cohorts and between cohorts with healthy controls, to estimate impact of immunological aspects of disease and treatment on vaccine response. Recent data in immunocompromised patients on rheumatological disease modifying agents showed comparable immune cellular response to COVID-19 vaccine to controls, despite reduced rate of neutralising antibodies, suggesting potential heterogenous cellular and humoral immune response to vaccine in immunocompromised patients [48]. PBMCs will also be analysed for epigenetic markers of T cell dysfunction, effector status, and exhaustion.

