#### Serological response

In the cancer setting, 2 large prospective trials have been presented at the European Society of Medical Oncology (ESMO) congress (September 2021) [20, 21]. These studies found high seroconversion rates to SARS-CoV-2 vaccination in adult patients with cancer (The VOICE study, 83–93% depending on arm [20], the CAPTURE study, 78% [21]). The CAPTURE study included haematological malignancies and found lower rates of seroconversion in this group. Lower rates of neutralising antibodies were noted to variants of concern. Both studies have so far only reported follow up until 2–4 weeks post second vaccine dose. Previously published studies have focused on short term serologic and immunologic response to vaccination in relatively small cohorts with diverse patient characteristics. Early evidence suggests a possible influence of treatment modality and cancer type upon antibody response, with impairment noted in those with haematological malignancies or receiving myelosuppressive treatments such as chemotherapy. In addition, these data confirm the importance of a second (boost) vaccine dose in cancer patients as critical to achieve improved antibody response to the vaccine. Summarised data is included in Table 1.

**Table 1 Tab1:** Summary of seroconversion rates and T cell responses amongst patients with cancer and healthy adults

	Seroconversion post 1 dose	Seroconversion post 2 doses	T cell response	Modifying factors
Solid organ cancer patients	38–83% [22, 24, 49, 50]	84–98% [20, 21, 24, 25, 49]	71% [24]	Use of steroids [24] Combined chemoimmunotherapy [23, 24]
Haematological malignancies	18–72% [24, 49, 51]	60–85% [20, 21, 24, 25, 27, 49]	50% [24]	Anti CD20 treatment [25] Stem cell transplant [25] BCMA targeted therapy [27] Anti CD38 regimens [27] Disease response [51]
Healthy adults	100% [28, 52]	100% [28, 52]	94% [28]	Age [28]

Detectable anti-Spike antibodies

*BCMA* B cell maturation antigen

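### Between-group differences in the antibody/T-cell correlation may reflect titre spread rather than disease or treatment, and the correlation does not measure the discordance the plan cites as motivation

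*Protocol article*

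**What the plan says.** The Analyses section of the protocol article names one analysis that links the two arms of immunity: "Correlation of magnitude of serological response and T-cell assays will be described within study cohorts and between cohorts with healthy controls". The same sentence gives its purpose: "to estimate impact of immunological aspects of disease and treatment on vaccine response". The word magnitude there belongs to the serological response, that is, to titre. No coefficient and no test between correlations is named.

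The next sentence reports that immunocompromised rheumatology patients had a cellular response comparable to controls but fewer neutralising antibodies, "suggesting potential heterogenous cellular and humoral immune response to vaccine in immunocompromised patients".

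The core assays are "qualitative and quantitative serologic assays and T-lymphocyte immune cell assessment", so a titre and a yes/no result will both be available. The section on sample size and statistical analysis says of the T-cell correlates that "this analysis has not been subject to formal statistical planning", and that group comparisons by t-test or analysis of variance "will be for the purpose of hypothesis generation".

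Table 1 ("Summary of seroconversion rates and T cell responses amongst patients with cancer and healthy adults") gives, after two doses:
- healthy adults: 100% seroconversion, 94% T-cell response
- solid organ cancer: 84–98% and 71%
- haematological malignancy: 60–85% and 50%

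Its footnote defines the serological measure as "Detectable anti-Spike antibodies".

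**The concern.** The stated purpose asks more of a correlation than it can give. A correlation mixes two things: how T-cell response changes with titre, and how much titre varies in the group. A cohort that contains non-responders can have a wider titre distribution than a control group in which nearly everyone responds. The correlations may then differ although the relation is the same. If the difference were read as the effect of disease or treatment, it could suggest altered coupling of humoral and cellular immunity where there is none.

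The second problem is a mismatch with the motivation. Preserved cellular with reduced humoral response is a share of patients: antibody-negative but T-cell-positive. A correlation does not give that share.

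Immune correlates are listed as co-primary in the endpoints paragraph of Study design, so the description will probably be read with some weight even though it is hypothesis-generating.

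**Working it through.** The article gives no figure for any correlation, so there is none to reproduce. Only the seroconversion and T-cell rates below come from the article. All SDs, slopes, gaps, assay limits and underlying correlations are assumptions.

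**1. Same relation, different spread.** Let T-cell response = a + b × log10 titre + error, with the same b and residual SD e in both groups. Then r = b·s / √(b²s² + e²), where s is the titre SD. Take b = e = 0.5.
- s = 0.3: r = 0.15 / √(0.0225 + 0.25) = 0.29
- s = 0.9: r = 0.45 / √(0.2025 + 0.25) = 0.67
- s = 0.4 v 0.5: r = 0.37 v 0.45
- equal s: equal r

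**2. Do the article's rates make unequal spread plausible?** Suppose a proportion p respond with titre SD 0.4, non-responders are recorded at a single value g log10 below the responder mean, and everyone lies on the line in step 1. The titre variance is p × 0.16 + p(1 − p)g². With b = e, r = √(variance / (variance + 1)).

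| Seroconversion | g = 1 | g = 1.5 | g = 2 |
|---|---|---|---|
| 100% (healthy) | 0.37 | 0.37 | 0.37 |
| 85% (top of haematological range) | 0.46 | 0.55 | 0.63 |
| 60% (bottom of haematological range) | 0.50 | 0.62 | 0.72 |

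For example, at 60% and g = 1.5 the variance is 0.096 + 0.540 = 0.636, and r = √(0.636 / 1.636) = 0.62. At 98%, the top of the solid organ range, the same gap gives variance 0.1568 + 0.0441 = 0.2009 and r = 0.41, close to the control value.

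**3. Is the direction fixed?** No. Let the cancer-cohort r be 0.50 and let u be the ratio of healthy to cancer titre SD, with the same line. Then the healthy r is 0.5u / √(0.75 + 0.25u²).
- u = 0.5: 0.28
- u = 0.75: 0.40
- u = 1: 0.50
- u = 1.5: 0.66

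Three simulations, each with equal SDs before any censoring and an uncensored r of 0.50, add to this:
- A healthy mean 1 SD higher, with no assay limit: 0.50 v 0.50.
- An upper assay limit that censors 50% of healthy titres: healthy 0.43 v cancer 0.485.
- A lower detection limit with 95% of healthy and 60% of cancer titres detectable: healthy 0.50 v cancer 0.45, the opposite direction.

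**4. Correlation against discordance.** Take a bivariate normal with underlying correlation 0.5 and cut each axis at the stated rate.

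| Seroconversion / T-cell response | Antibody−, T-cell+ | Both negative |
|---|---|---|
| 95% / 94% (control rate assumed for sample size; Table 1 T-cell rate) | 4% | 1% |
| 85% / 50% (haematological) | 3% | 12% |
| 60% / 50% (haematological) | 12% | 28% |

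One underlying correlation is thus compatible with clearly different shares, so the shares have to be reported in their own right.

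**5. How well does a slope comparison behave?** With s = 0.3 v 0.9, 100 per group, the line in step 1 and titre measured without error, a test of equal slopes rejects in about 5% of simulated studies. Titre error of SD m shrinks each slope by s²/(s² + m²). At m = 0.2 the slopes become 0.35 v 0.48 and rejection rises to about 14%. At m = 0.3 they become 0.25 v 0.45 and it rises to about 32%.

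**The case against.** The strongest reply is that the article promises only description. It plans no test between correlations, calls the T-cell comparisons hypothesis-generating, and may leave coefficients and models to the full protocol or analysis plan. All of that stands. It limits the weight of the point but does not remove it, because the article itself fixes both the quantity and the inference to be drawn from it.

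A reader might infer more than the documents support, in three ways.
- **That healthy controls will show the weaker correlation because they sit at an antibody ceiling.** Table 1 reports detectable antibody, a yes/no measure, so 100% does not show that titres are compressed. No titre SD or upper assay limit is given. The background reports titres in solid-tumour seroconverters as similar to controls in some studies and lower in others. Step 3 shows that the difference can vanish or reverse.
- **That the plan carries a high false-positive rate.** A Fisher-z comparison at 100 v 100 would flag the 0.29 v 0.67 difference in about 95% of studies: z difference 0.513 / √(2/97) = 3.57. At SD 0.4 v 0.5 it would do so in only about 10%, and the plan contains no such test.
- **That discordance in these cohorts is as high as 32%.** That needs 60% seroconversion with 90% T-cell response, a pair found nowhere in the article. The haematological pairs give 3% to 12%.

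It is also fair to say that nothing rules out a cross-tabulation, and that regression is not immune to spread (step 5). Regression is better than comparing correlations but still needs a caution.

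**Conclusion.** The point holds in a limited form. A between-group difference in the antibody/T-cell correlation cannot by itself be read as an effect of disease or treatment, because the correlation also moves with titre spread. Unequal spread is plausible where many patients do not respond, above all in haematological malignancy. Under the assumptions of step 2, an identical relation gives 0.37 in controls and 0.46 to 0.72 at the haematological seroconversion rates. For solid-tumour cohorts near the top of their range the difference may be negligible. Direction and size cannot be fixed from the article. Separately, the correlation does not measure the preserved-cellular, reduced-humoral pattern given as motivation. No confirmatory conclusion is at stake, so this is a worthwhile, inexpensive improvement to a hypothesis-generating analysis.

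**What to change.** Keep the within-cohort correlations as description, and state that differences in r between groups will not be read as disease or treatment effects. For the between-group description at 1 month after the second dose, report:

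1. For each cohort and for controls, the two-by-two table of antibody positive/negative by T-cell positive/negative. Give differences from controls in the antibody-negative/T-cell-positive and double-negative shares, with 95% confidence intervals, using a prespecified T-cell cut-off.
2. Titre SDs by group, and a regression of T-cell response on log titre with a group term and group-by-titre slopes, with confidence intervals. Say how titres outside the assay limits are handled, and caution that titre measurement error can also make slopes differ.

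The cost is analysis wording only, on the same samples and assays. The one real demand is that a T-cell positivity cut-off be fixed before the data are examined.
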